**Figure 1 figure1:**
[figure not shown]
Intervention arms and data collection time-points.

### Participant Eligibility Criteria

Individuals will be eligible to participate if they: are 18 years or older; have a primary diagnosis of any lung cancer type (including mesothelioma); are less than 4 months post diagnosis; have an approximate life expectancy of at least 6 months; and have current Internet access via any type of device including shared access or public access (eg, via a family member or public library).

### Patient Recruitment and Consent Procedure

Eligible lung cancer outpatients will be identified and approached by health professionals (care coordinators, nurses, or clinicians) and will be recruited in 1 of 3 ways:

Full consent process completed in clinic settings immediately: during patients’ appointments, clinic staff or a research assistant (depending on the clinic’s preference) will ask the patient whether they have Internet access, provide study information materials to eligible patients (including a baseline survey), and invite them to participate in the study. Participants will complete a written consent form in clinic and can choose to complete the survey in-clinic or at home.

Consent for further contact completed in clinic settings immediately, with full consent process completed by a research team member: during patients’ appointments, clinic staff will ask whether they have Internet access and if they would be interested in being contacted by the research team regarding the study. Interested patients will complete a consent form that allows the clinic to forward the patient’s contact details to the research team. Once consent forms are forwarded to the research team, patients will be contacted via their preferred mode of contact to discuss possible study participation. Up to 2 follow-up contacts will be made to nonrespondents. Patients who would like to participate will complete a separate consent form, which will be posted along with the baseline survey.

Full consent process completed outside of the clinic setting by a health professional: health professionals, typically care coordinators, will mail information booklets and make follow-up telephone calls to patients as part of standard care procedures. As part of these standard contacts, study materials (information statement, consent form, and baseline survey) will be included in the mail-out package, and the health professional will discuss the study when making calls to patients.

### Randomization Process and Blinding

Stratified block randomization will be completed by the research team using a Web-based random number generator program immediately upon receiving a completed consent form. All participants will complete the baseline survey prior to randomization. Randomization will be by patient, with analyses accounting for clustering of outcomes by CIS consultant. The randomized list of patients will then be given daily to the CIS service to contact participants using the allocated approach method (mailed booklet, telephone call, or email/live chat). Due to the nature of the interventions, patients and CIS consultants will not be blinded to the allocation arm; health professionals will not be informed of participants’ allocation. Those responsible for data analysis and interpretation will be blind to group allocation. There is no foreseeable circumstance in which revealing a participant's group allocation to data analysts would be required.

### Interventions

Participants will be randomized to 1 of 3 arms: (1) a booklet from the Cancer Council which contains the CCNSW CIS service details (minimal ethical care (control)), (2) phone call(s) from the CCNSW CIS service (proactive telephone-delivered support), or (3) email(s) and live chat consultation from the CCNSW CIS service (proactive Web-delivered support). See Figure 1 for brief description with data collection time-points.

#### Arm 1: Minimal Ethical Care (Control)

Patients will be mailed a booklet (“Understanding Lung Cancer”) from the CCNSW. The booklet will contain the CIS service telephone number and email address. Although lung cancer accounts for 9% of all new cancers diagnosed, lung cancer patients account for only 1% of calls received by the CIS service. Therefore, it is not expected that a high proportion of the control group will contact the service independently. Any potential contamination via calls to the CIS service from this group will be identified using questions in the follow-up survey and by reviewing internal CIS records.

#### Arm 2: Proactive Telephone-Delivered Support

The CIS model is tailored to callers’ needs rather than following a manualized protocol as may be the case for delivery of some therapies such as CBT. The patient consent form will request contact details and preferred times to call. The research team will provide this information to the CCNSW CIS service and patients randomized to this intervention arm will receive a 20-50 minute outbound call from a trained consultant within a few days of the CIS service receiving their contact details. The CIS consultant will make multiple attempts (up to 5 calls made at varying times and weekdays) to establish contact with the patient. Following the initial discussion, the CIS consultant will also offer an additional, subsequent call-out. Following the completion of the 2 proactive calls from the CIS, patients in this group can initiate further contact if desired.

##### Call Content

Call content will reflect usual care and will follow the CIS model, in which the call is guided by patients’ individual needs with 3 main types of support available: informational, emotional, and instrumental. Emotional support involves communication of caring and concern, and is argued to reduce distress by improving self-esteem and encouraging the expression of feelings [34,35]. Informational support is thought to enhance perceptions of control by reducing confusion and providing patients with strategies to cope with their difficulties [34,35]; in addition to the verbal information exchanged over the course of a call, specific examples of the informational support provided by the CIS includes: reference to Web-based videos and Web seminars; provisions of paper-based information packages; and access to a cancer service directory. Instrumental support involves the provision of tangible goods such as transportation, money, or physical assistance and leads to a decrease in feelings of loss of control [34,35]. Specific examples of instrumental support offered by the CIS service includes: linking callers with services in their local area; financial grants; transportation grants; and subsidized accommodation. CIS service manuals detailing the 3 main types of support are available upon request. Repeated contact with the same CIS consultant is preferred but not always achieved as a matter of course.

#### Arm 3: Proactive Web-Delivered Support.

Participants allocated to this intervention arm will be contacted within a few days of randomization via email and a hard copy letter. The letter and email will explain the available electronic options for support (email delivered or Web-based typed live chat) and provide the study-specific Web-link needed for intervention access. Participants will be able to use either or both modes of electronic contact according to their preference. If participants have not engaged with either electronic option within 2 weeks of allocation, subsequent telephone calls (up to 5 calls made at varying times and weekdays) will be conducted by the research team to confirm the participant has received the information and to provide additional instructions if needed.

Usual CIS service content (as described above) will be provided via typed rather than spoken communication, using email and Web-based chat. Equivalence of telephone- and Web-delivered content and quality will be examined via 5-10 simulated clients using standardized vignettes. These telephone and Web conversations will be transcribed. The transcriptions will BE reviewed by senior research team members with the content compared with a quality checklist developed in collaboration with CIS representatives according to their current evaluation practices. This process will occur at 3 time-points in the intervention phase and will also serve as a fidelity measure. To ensure the majority of consultants are included in this equivalence test, it may be necessary to complete up to 10 simulations.

CIS consultants will receive training and a detailed manual on the features of the Web system, including ways to convey emotional support, such as empathetic responses using typed text. This manual is available upon request. Multimedia Appendices 1 and 2 provide screenshot examples of the instructions and simulated Web-based chat conversation between a member of the research team and CCNSW consultant. Following their first electronic session, participants will be offered an additional email contact from the CIS service. Similar to the other intervention arm, participants in this group can initiate further electronic contact if desired. Continuity of care (ie, contact from the same consultant) may not always occur. Any potential contamination via calls to the CIS service from the Web-support group will be identified using questions in the follow-up survey and by reviewing internal CIS records.

##### Measures

The baseline and follow-up measures listed below will be collected via pen-and-paper surveys; this data will be securely stored according to approved procedures. The follow-up points for patients will be 3 and 6 months post recruitment, as approximately 60% of lung cancer patients have a life expectancy of less than 12 months [2]. Participants who do not return a survey within 2 weeks will receive a reminder letter and an additional survey package. A research team member will telephone nonresponders 2 weeks following the first reminder letter. All survey variables, including data collection time-points, are listed in Table 1.

**Table 1 table1:** Study data and associated variables collected at each study time-point.

		Time-point		
Study data	Variables	Baseline	3 months	6 months
**Primary outcomes**				
	GHQ-12; heiQ	X	X	X
**Secondary outcomes**				
	SCNS-34^a^ subscales (health systems and information; patient care and support)	X		X
**Process measures**				
	Five items exploring contact and satisfaction with CIS^b^ services; perceived level of consultant skill; and use of specific CIS services (emotional; information; instrumental)			X
**Demographic characteristics**				
	Age at diagnosis; sex; Aboriginal or Torres Strait Islander origin; health insurance coverage; employment status; post code; marital status; highest level of education attained; primary language spoken at home; and concession card holder	X		
**Emotional adjustment**				
	The Mental Adjustment to Cancer Scale [36]	X		
**Disease/treatment**				
	Date of cancer diagnosis; cancer type; other comorbid conditions; surgery and treatments received; and history of mental health treatment prior to cancer diagnosis	X		
	Current extent of cancer; surgery and treatments received; and instances of missed prescriptions in previous week		X	X
**Smoking history**				
	Current smoking status; previous referral and uptake of smoking cessation assistance; and smoking quit date	X		
	Smoking status within the last 6 months			X
**Social support**				
	Medical Outcomes Study-Social Support Survey [37]	X		X
**Illness appraisal**				
	Brief Illness Perception questionnaire [38]	X		X
**Health service utilization**				
	Stanford Health Care Utilization tool [39]			X

^a^SCNS-34: 34-item Supportive Care Needs Survey.

^b^CIS: Cancer Information and Support.

##### Primary Patient Outcomes

The GHQ-12 is a widely used, self-report screening measure of general psychological distress [40]. The 12-item measure takes 2 minutes to complete and assesses an individual’s perception of their health in terms of their ability to: play a useful part; make decisions; overcome difficulties; enjoy normal activities; face problems; and to feel confident, worthwhile, and happy [41]. The time-frame of the GHQ-12 covers the last 4 weeks and items are scored using a 4-point scale (“better than usual,” “same as usual,” “less than usual,” and “much less than usual”) [42]. Half of the items are worded positively, and the other half negatively. Items can be scored using either a Binary scale (0-1, maximum score = 12) or Likert scale (0-3, maximum score = 36), with a higher score indicating higher psychological distress [42]. The GHQ-12 has excellent internal consistency (Cronbach’s alphas above 0.82 for cancer patients) and test-retest reliability [41]. The measure has also been validated in the general Australian community and with cancer populations, including patients with a history of lung cancer [41-44].

Participants who indicate severe levels of distress (scores > 20 on the GHQ-12) at either the baseline, 3, or 6 months survey will be mailed a letter encouraging them to discuss their feelings with their doctor. Contact details of available support services will also be provided.

The heiQ is an Australian-developed tool for assessing the efficacy and impact of health education and self-management programs for people with chronic diseases [45]. Its 42 items are closely aligned to the nature of the CIS service and map to 8 domains: (1) health-directed behavior, (2) positive and active engagement in life, (3) emotional well-being, (4) self-monitoring and insight, (5) constructive attitudes and approaches, (6) skill and technique acquisition, (7) social integration and support, and (8) health service navigation. Respondents indicate the degree to which they agree or disagree with each item on a 4-point scale. Standardized subscale scores (from 1-4) are calculated, with higher scores indicating better functioning.

The heiQ was developed using Structural Equation Modelling and Item Response Theory. It has demonstrated reliability and validity among people with a wide range of chronic diseases and demographic characteristics and sensitivity to change as a result of intervention [45,46].

##### Secondary Patient Outcome

Two subscales of the 34-item Supportive Care Needs Survey (SCNS-SF34) will be used to assess unmet needs [47]. The scale assesses cancer-specific perceived needs across 5, factor analytically derived domains. The 2 relevant domains for this study are: (1) health systems and information, and (2) patient care and support [47]. Respondents indicate their level of need for help over the last month on a 5-point Likert scale. Standardized domain scores ranging from 0 to 100 can be calculated. The SCNS-SF34 has Cronbach’s alphaS greater than 0.86 for each subscale, and is moderately correlated with other measures of psychosocial morbidity [47].

##### Patient Process Measures

Process data will include: number of contacts made to and received from the CIS service; utilization of specific information and support services; acceptability of the information and support provided; and perceived skill level of the CIS consultant. All participants will provide this information at 6 months. Excepting initial telephone calls to participants who do not engage with one of the Web-delivered support options within 2 weeks of group allocation, no additional strategies will be used to increase use of the telephone or Web arms as uptake rates (with consideration of differential use by demographic characteristics) is an important indicator of the intervention acceptability.

##### Antecedent and Moderating Factors

Participants will complete additional survey items to account for sociodemographic, disease and treatment, and social support characteristics, which may moderate the intervention effects. Table 1 outlines these survey items, along with all study data items, and the time-point at which this information will be collected.

### Sample Size

The sample size calculation is based on the post-hoc contrasts. The comparison of each intervention group with minimal ethical care is a superiority analysis, whereas the comparison of the 2 intervention arms of the study is a noninferiority analysis.

The study aims to recruit 501 subjects, and therefore complete data will be available for approximately 375 patients (125 per arm) at 6 months with an estimated 25% (125/501 participants) lost to follow-up. This sample size will provide the study with more than 80% power to detect a difference between each of the intervention groups and the control group of 0.35 SD at an alpha level of 0.01 assuming the correlation between baseline and follow-up scores is at least 0.7. This sample size will also provide the study with 90% power to claim noninferiority in the comparison between the 2 interventions if the true underlying difference between the groups is 0.29 SDs for either the heiQ or GHQ-12. A meta-analysis of Web-based emotional support reported an average effect size of approximately 0.4 across 15 studies [48]; similarly, previous research found modest effect sizes of 0.3-0.5 on the heiQ in self-management interventions in Australian and hospital-based samples [49,50]. The age group and gender of nonparticipants will be compared with that of participants to assess nonconsent bias.

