In the context of the CIS service, the most appropriate first step for testing Web approaches may be via a proactive and personalized, rather than automated, version of the service through email and live chat. Email counseling involves the patient and counselor exchanging questions and responses at the frequency of their choosing over the Internet. Live chat involves typed interactive conversations occurring in real-time over the Internet. Evidence for online peer-support forums and email is promising with a RCT of a multicomponent Web intervention reporting decreased global severity scores in a sample of 325 breast and prostate cancer patients [31]. However, there is no literature regarding Internet-delivered versions of low-intensity community-based support akin to that offered by the CIS service. For example, a Cochrane review examining the effects of email and Web-messaging between patients and health professionals was unable to establish the benefits of such Web-based platforms due to the lack of high-quality studies identified [32]; relevant to this study, none of the 9 reviewed articles included cancer samples.

This multisite, blinded, patient-RCT will be the first to conduct a robust study of the relative merits of telephone- versus Web-based methods for providing low-intensity information and support to people affected by cancer. Newly diagnosed lung cancer patients will be recruited by health professionals and randomly-allocated on a 1:1:1 ratio to 1 of 3 arms: (1) a printed information booklet, (2) proactive telephone-delivered support, or (3) proactive Web-delivered support. The Consolidated Standards of Reporting Trials of Electronic and Mobile HEalth Applications and onLine TeleHealth is used to describe this study [33].

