### Statistical Analysis

Primary analysis will compare scores on the GHQ-12 and 5 key heiQ dimensions (emotional support and well-being; monitoring and insight; constructive attitudes; skill acquisition; health service navigation) at a 6-month follow-up across the 3 groups. Differences between treatment groups on each of GHQ-12 and heiQ scores at the 6-month follow-up will be tested using analysis of covariance. The outcomes in the models will be the GHQ-12 score and heiQ score of interest at 6 months, the main predictor of interest will be treatment group and the baseline value of the GHQ-12 score and heiQ score will be included as covariates. Three post-hoc contrasts will be carried out; the first 2 of these will compare separately each of the intervention groups with the control group and the third will compare the proactive telephone-delivered support with the proactive Web-delivered support. To account for Type I error in the post-hoc analyses, Bonferroni corrections will be applied.

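### The 90% noninferiority power is reached only without the Bonferroni correction the plan applies; over three contrasts, at the planning correlation of 0.7, it is about 79% to 86%.

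*Protocol article*

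**What the plan says.** The Sample Size section of the protocol article says that the calculation rests on the post-hoc contrasts. It treats each intervention against control as superiority and the two interventions against each other as noninferiority. It expects that "complete data will be available for approximately 375 patients (125 per arm) at 6 months". For superiority it claims power above 80% for "0.35 SD at an alpha level of 0.01 assuming the correlation between baseline and follow-up scores is at least 0.7". The next claim is "This sample size will also provide the study with 90% power to claim noninferiority in the comparison between the 2 interventions", tied to 0.29 SD on either the heiQ or the GHQ-12. That sentence gives neither an alpha nor a sidedness.

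The Statistical Analysis section specifies analysis of covariance with the baseline score as covariate and lists three post-hoc contrasts. The third is telephone versus Web. It then says "To account for Type I error in the post-hoc analyses, Bonferroni corrections will be applied". No contrast is exempted, and neither the divisor nor the starting alpha is given.

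**The concern.** A power figure is valid only at the significance level at which the test will be carried out. Here the power claim and the correction rule concern the same contrast, and the power claim appears to ignore the rule. Whether Web support is comparable to telephone support is the second of the trial's two aims and its second hypothesis. If the corrected level is used, the chance of failing to show noninferiority between two truly identical modes is larger than the 10% a reader would take from the article, and an inconclusive result would be judged against power the trial does not have. The text also leaves open whether the noninferiority bound is a corrected or an uncorrected one. That choice could decide the conclusion and should be settled before the data are analysed.

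**Working it through.** **Inputs**
- Completers per arm: 125 (Sample Size), with 1:1:1 allocation (Background).
- Correlation between baseline and 6 months: at least 0.7. It is stated in the superiority sentence and carried over here as an assumption. The floor of 0.7 is used.
- Model: ANCOVA (Statistical Analysis).
- Margin 0.29 SD, true difference 0. The Sample Size sentence actually describes 0.29 SD as the true difference, while the Hypotheses section uses it as the limit of comparability. The second use is the one that makes a power calculation possible.
- Alpha for noninferiority: not stated, so several levels are tried.

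**Formulae**

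SE of the contrast = √(1 − 0.7²) × √(2/125) = 0.7141 × 0.1265 = 0.0903 SD.

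Margin/SE = 0.29/0.0903 = 3.21.

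Power = Φ(3.21 − z), where z is the one-sided critical value.

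**The plan's figure first, then the corrected levels**

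| One-sided level | z | Power | Below 90% by |
|---|---|---|---|
| 0.05, uncorrected | 1.645 | 94.1% | – |
| 0.025, uncorrected | 1.960 | 89.4% | 0.6 points |
| 0.05/3 | 2.128 | 86.0% | 4.0 points |
| 0.025/3 | 2.394 | 79.3% | 10.7 points |
| 0.01 (if the superiority alpha applied, one-sided) | 2.326 | 81.2% | 8.8 points |
| 0.005 (if the superiority alpha applied, two-sided) | 2.576 | 73.7% | 16.3 points |

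The noncentral t distribution with 371 degrees of freedom lowers each figure by less than half a point.

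The chance of missing noninferiority when the modes are identical is therefore 14% at 0.05/3 and 21% at 0.025/3.

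**What would restore 90%**

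Correlation needed at 125 per arm: r = √(1 − (0.29/(z + 1.282))² × 125/2). This gives 0.74 at 0.05/3, 0.78 at 0.025/3, 0.77 at 0.01 and 0.80 at 0.005.

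Completers per arm needed at r = 0.7: 2 × 0.51 × ((z + 1.282)/0.29)². This gives 141 at 0.05/3 and 164 at 0.025/3, against 125 planned.

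**Superiority check**

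0.35/0.0903 = 3.87, and Φ(3.87 − 2.576) = 90%, which agrees with the claim of more than 80%.

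**Alternative variance**

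With a change-score analysis the SD is √(2 × (1 − 0.7)) = 0.775. Noninferiority power is then 90.6% at one-sided 0.05, 79.7% at 0.05/3 and 71.4% at 0.025/3. Again, 90% appears only at an uncorrected level.

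**The case against.** The strongest reply is that an article may leave the noninferiority alpha, its sidedness and the Bonferroni family to the full protocol or the SAP, neither of which is shown. That stands as far as missing detail goes. It does not remove the mismatch between a power figure and a correction rule that the article does state.

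A second reply is that the correlation is assumed to be at least 0.7, so the powers above are the lower end of the plan's assumption. That is true, and values of 0.74 to 0.80 would bring back 90%. But 0.7 is the value the plan gives, and a claim resting on a floor should hold at the floor.

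Three stronger readings are tempting, and the document does not support them:
- A reader might infer that 0.01 is the plan's alpha for this contrast too, so that power is 74% to 81%. The 0.01 is attached to the comparisons with control only. It also does not equal 0.05/3, so it cannot simply be taken as the Bonferroni level.
- A reader might infer that the 90% can come only from one-sided 0.025. One-sided 0.05 also reaches it, with ANCOVA or with change scores.
- A reader might infer that the match on superiority reveals the sponsor's inputs. More than 80% is a loose bound. The change-score variance also satisfies it (84% at two-sided 0.01), so the inputs are not identified.

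**Conclusion.** The stated 90% does not hold under the analysis as described. At the planning floor of r = 0.7, with 125 completers per arm, a 0.29 SD margin and no true difference, a three-contrast Bonferroni correction gives 86% if it starts from one-sided 0.05 and 79% if it starts from one-sided 0.025. The overstatement is about 4 to 11 points. It would be up to about 16 points if 0.01 two-sided also governed this contrast, but that is a conditional figure, not something the document says.

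The result rests on reading 0.29 SD as the margin, in the sponsor's favour, and on carrying the correlation over from the superiority sentence. It shows a power statement to be corrected. It does not show that the design is unsound or that recruitment must rise.

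**What to change.** In the Sample Size section, state the noninferiority margin, the assumed true difference and the one-sided alpha together, and restate the power at the level the Statistical Analysis section will use: about 79% at one-sided 0.025/3, or about 86% at one-sided 0.05/3.

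Alternatively, say in the Statistical Analysis section that telephone versus Web lies outside the Bonferroni set and is tested at one-sided 0.025. The power is then about 89%, and the existing claim nearly stands.

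Either change should be made before the data are analysed. It costs one sentence and, on the first route, a less favourable figure. No extra patients or data are needed.

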### Hypotheses

It is hypothesized that at 6 months follow-up: (1) those in the 2 experimental conditions (proactive telephone-delivered or Web-delivered support) will have GHQ-12 scores that are 0.3 of a standard deviation (SD) lower than those for the control condition and heiQ scores that are 0.3 of a SD higher than those for the control condition, and (2) those in the proactive Web-delivered support condition will have heiQ scores within 0.29 of a SD of those in the proactive telephone-delivered support condition.

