## Results

It is hypothesized that participants receiving telephone or Web support will report reduced distress and greater self-efficacy than participants receiving booklets. Furthermore, individuals receiving Web support will report heiQ scores within 0.29 SDs of individuals receiving telephone support. Participant recruitment is underway and will conclude in September 2017.

This study has been approved by the Hunter New England Human Research Ethics Committee (NHMRC Committee Code: EC00403; Reference No. 14/05/21/4.03); the University of Newcastle Human Research Ethics Committee (NHMRC Committee Code: EC00144; Reference No. H-2014-0240); and, the Cancer Council of New South Wales (NHMRC Committee Code: EC00345; Reference No. 291). The study has also been approved by local research governance committees at each participating health service. This trial was registered with the Australian New Zealand Clinical Trials Registry (ACTRN12615000932561) and received funding from the National Health and Medical Research Council as a Partnership Project.

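### The noninferiority power statement gives the 0.29 SD margin as the true difference; 90% cannot hold there, and the figure is also too high if the plan's Bonferroni rule covers this contrast

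*Protocol article*

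**What the plan says.** The Sample Size section says that "the comparison of the 2 intervention arms of the study is a noninferiority analysis". It expects that "complete data will be available for approximately 375 patients (125 per arm) at 6 months", "with an estimated 25% (125/501 participants) lost to follow-up". For the two superiority contrasts it gives more than 80% power to detect "0.35 SD at an alpha level of 0.01", assuming a baseline to follow-up correlation of at least 0.7. For noninferiority it claims "90% power to claim noninferiority in the comparison between the 2 interventions if the true underlying difference between the groups is 0.29 SDs", on either the heiQ or the GHQ-12. That sentence gives no margin, alpha or correlation of its own.

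The same 0.29 SD has a different role elsewhere. Under Hypotheses, Web participants "will have heiQ scores within 0.29 of a SD of those in the proactive telephone-delivered support condition". The Results section repeats that "individuals receiving Web support will report heiQ scores within 0.29 SDs of individuals receiving telephone support", and so does the Results paragraph of the abstract. All three places give the limit for the heiQ only; the Sample Size section alone extends 0.29 SD to the GHQ-12.

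The Statistical Analysis section specifies ANCOVA of the 6-month score on treatment group and baseline. It lists three post-hoc contrasts, the third being telephone versus Web, and says: "To account for Type I error in the post-hoc analyses, Bonferroni corrections will be applied". It makes no exception for the third contrast.

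**The concern.** A noninferiority test needs two separate quantities: the margin, which is the largest deficit still accepted, and the true difference at which power is evaluated. The article has one number, 0.29 SD. The Hypotheses and Results sections use it as the margin, and the Sample Size section uses it as the true difference. Taken together, they place the truth on the boundary of the null hypothesis, where the test is built to claim noninferiority only rarely.

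This is the only power given for the second of the study's two aims. A reader who takes it at face value would believe that the trial is very likely to declare Web support noninferior when it is in fact worse by the whole margin.

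A second question follows once the sentence is read as it was probably meant: whether 90% agrees with the multiplicity rule that the article sets for the same contrast.

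**Working it through.** **Inputs from the article**
- 125 analysed per arm (Sample Size).
- Margin m = 0.29 SD (Hypotheses, Results).
- ANCOVA with baseline as covariate (Statistical Analysis).

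**Assumptions**
- Correlation r = 0.7, carried over from the superiority sentence.
- One-sided alpha for noninferiority, which is not stated and is therefore varied.
- Bonferroni divisor of 3, for the three listed contrasts; the article does not give the divisor.

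**Standard error** of the adjusted difference, in SD units:

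SE = sqrt((1 − r²) × 2/n) = sqrt((1 − 0.49) × 2/125) = sqrt(0.00816) = 0.0903

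**Power**, for true deficit d and one-sided alpha a:

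Power = Φ((m − d)/SE − z(1−a))

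**Step 1: reproduce the printed 90%.** Take 0.29 SD as the margin and d = 0. Then 0.29/0.0903 = 3.210. At a = 0.025, Φ(3.210 − 1.960) = Φ(1.250) = 89.4% (89.2% with a noncentral t). This is close to 90%.

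**Step 2: the sentence as printed.** With d = m = 0.29, the first term is zero and power = Φ(−z(1−a)) = a, whatever the sample size or correlation:

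| One-sided alpha | Probability of claiming noninferiority at d = 0.29 SD |
|---|---|
| 0.05 | 5% |
| 0.025 | 2.5% |
| 0.01 | 1% |
| 0.005 | 0.5% |

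For 90% power at a true deficit of 0.29 SD with one-sided 0.025, the margin would have to be 0.29 + 0.0903 × (1.960 + 1.282) = 0.29 + 0.293 = 0.58 SD. The article contains no such margin.

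**Step 3: the intended reading under the multiplicity rule.** Margin 0.29 SD, d = 0:

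| Alpha for this contrast | One-sided alpha | Calculation | Power |
|---|---|---|---|
| 0.05 two-sided, uncorrected | 0.025 | Φ(3.210 − 1.960) | 89.4% |
| 0.05/3 taken as one-sided | 0.0167 | Φ(3.210 − 2.128) | 86.0% |
| 0.01 taken as one-sided | 0.01 | Φ(3.210 − 2.326) | 81.2% |
| 0.05/3 two-sided | 0.0083 | Φ(3.210 − 2.394) | 79.3% |
| 0.01 two-sided | 0.005 | Φ(3.210 − 2.576) | 73.7% |

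Every corrected level gives less than 90%.

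**Step 4: is the route to 90% unique?** No. With a change-score variance and r = 0.7, SE = sqrt(2(1 − 0.7) × 2/125) = sqrt(0.0096) = 0.0980. At one-sided 0.05 this gives Φ(2.960 − 1.645) = 90.6%. The article specifies ANCOVA, so this is not its stated analysis, but it shows that the alpha behind the 90% cannot be recovered with certainty.

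**The case against.** The strongest defence is that this is a slip of wording. The Hypotheses and Results sections make the role of 0.29 SD clear, an informed reader will treat it as the margin, and on that reading 125 per arm does give about 90% power at one-sided 0.025. The recruitment target, the model and the contrasts would not change. That is right about the sample size. It does not make the printed sentence true, and a fuller protocol or analysis plan could not do so either, because the article states an assumption rather than leaving one out.

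Some stronger readings are tempting, and the article does not support them:

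- **That the true power is 2.5%.** That figure assumes one-sided 0.025, which is stated nowhere. What holds is that the probability equals the one-sided alpha, whichever is used.
- **That 90% can arise only from one-sided 0.025 with r = 0.7.** Step 4 shows another combination that fits at least as well.
- **That an alpha of 0.025 contradicts the 0.01 of the superiority sentence.** The 0.025 is inferred from the 90%, so there are not two printed levels in conflict. The narrower point is that this contrast has no stated alpha, and that the Bonferroni rule as written lowers its power.
- **That the noninferiority contrast ought to be taken out of the Bonferroni family.** That is a design preference. Nothing in the article shows the inclusion to be wrong.

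**Conclusion.** The point holds. As printed, the noninferiority power statement is wrong at any conventional alpha: with the true difference at 0.29 SD and 0.29 SD the only candidate margin, the probability of claiming noninferiority is 0.5% to 5%, not 90%. This result needs no assumption about correlation or sample size.

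Read as margin 0.29 SD and true difference zero, the figure is about right (89.4%) only for a contrast tested at an uncorrected one-sided 0.025, given ANCOVA, r = 0.7 and 125 per arm. Under the article's own Bonferroni rule it is too high: about 79% at two-sided 0.05/3 and 74% at two-sided 0.01, or at most 86% if 0.05/3 is taken as one-sided.

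The error lies in the power statement and its specification. It does not show that the recruitment target was miscalculated. It should still be corrected, because no other power is stated for the second aim.

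**What to change.** Rewrite the noninferiority sentence in the Sample Size section so that it:

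1. names 0.29 SD as the noninferiority margin, and says whether it applies to the GHQ-12 as well as the heiQ;
2. gives zero as the assumed true difference;
3. states the alpha for this contrast with its sidedness, and the assumed correlation;
4. quotes the power that matches the multiplicity rule in the Statistical Analysis section: about 79% at two-sided 0.05/3, or 74% at two-sided 0.01. The 89% figure can stand only if the sponsor states that this contrast is tested at one-sided 0.025 outside the correction.

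The alpha is for the sponsor to state; it should not be inferred from the 90%. The cost is one or two sentences and, under the rule as written, a less favourable power figure. No extra patients are needed.
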